### Study Synopsis

| **Title** | **G**estati**o**nal **D**iabetes future **D**iab**E**te**S** prevention **S**tudy – feasibility trial |
| --- | --- |
| **Protocol Short Title/Acronym** | GODDESS |
| **Protocol Version number and Date** | Version-4  Date: 17/01/18 |
| **Study Phase if not mentioned in title** | N/A |
| **Is the study a Pilot?** | No |
| **Study Hypothesis** | The primary hypothesis (H^O^1) for the study is that a lifestyle intervention to increase physical activity and promote weight loss in women with recent gestational diabetes mellitus (GDM) is feasible |
| **Study Duration** | 18 months |
| **Methodology** | Feasibility randomised controlled trial (RCT) |
| **Sponsor name** | [name] |
| **Chief Investigator** | [name] |
| **REC number** | **177238** |
| **Medical condition or disease under investigation** | Risk of type two diabetes in women with previous gestational diabetes |
| **Purpose of clinical trial** | To test the feasibility of a trial to improve diet, increase physical activity and promote weight loss in women with recent GDM, with a view to preventing or delaying T2DM |
| **Primary objective** | To explore the acceptability of a lifestyle intervention to increase physical activity and promote weight loss in women with recent GDM, and test the feasibility of the trial |
| **Secondary objective (s)** | To assess preliminary efficacy of the intervention |
| **Number of Subjects/Patients** | 60 |
| **Trial Design** | Feasibility two-armed parallel group RCT |
| **Endpoints** | Once the primary outcome variables have been appropriately measured and data analysis completed, this marks the end of the study. |
| **Main Inclusion Criteria** | - aged ≥18 years - diagnosed with GDM (NICE cirteria) - ≤30 weeks pregnant - able to speak and understand English - body mass index (BMI) of ≥ 25kg/m^2^ (or ≥22 kg/m^2^ if Asian) |
| **Statistical Methodology and Analysis** | Feasibility will be assessed through the process evaluation.  For the preliminary efficacy outcomes, between group and group*time interactions will be used to estimate the intervention effects (analysis of variance). The analysis will be performed using SPSS by intention to treat. Further regression analysis will be used to adjust for any potential confounding factors not factored into the stratification. |

# Glossary of Terms and Abbreviations

BCT Behaviour change technique

CI Chief Investigator

CRF Case Report Form

GDM Gestational diabetes mellitus

MREC Main Research Ethics Committee

NHS R&D National Health Service Research & Development

PI Principle Investigator

QA Quality Assurance

QC Quality Control

Participant An individual who takes part in a clinical trial

RCT Randomised Controlled Trial

REC Research Ethics Committee

SAE Serious Adverse Event

SDV Source Document Verification

SOP Standard Operating Procedure

SSA Site Specific Assessment

TMG Trial Management Group

TSC Trial Steering Committee

T2DM Type 2 Diabetes Mellitus

### 1. Introduction

- 1. **Background**

GDM is a common condition, occurring in around 5% of pregnancies [1], and is increasing [2]. Women with GDM are over seven times more likely than women with normoglycaemic pregnancies to develop T2DM [3], and their risk is estimated at 30% within 5-16 years of pregnancy [4]. Compared to women with normoglycaemic pregnancies, women with GDM have a 30-84% increased chance of another episode of GDM [5], and children of women with diabetes in pregnancy are more likely to become obese or develop T2DM [6]. GDM is associated with adverse fetal, infant and maternal pregnancy outcomes [7], and T2DM is associated with increased morbidity and mortality [8].

- 1. **Prevention of T2DM in high-risk groups through lifestyle modification**

Large-scale studies have shown that T2DM can be prevented or delayed in high-risk populations through lifestyle modifications after psychological or educational interventions. Findings from the Diabetes Prevention Program (DPP) Research Group show that a lifestyle intervention reduced the incidence of diabetes in a high risk group by 58% [9]. Tuomilehto et al. [10] also found a 58% reduction in diabetes incidence after individualised lifestyle counselling in the intervention group compared to controls.

- 1. **Prevention of T2DM after GDM**

A sub-analysis of the DPP data showed that women with GDM (mean 12 years prior to the study) experienced a 50% reduction in incidence of T2DM after the lifestyle intervention [11]. However, other than this, little research has been conducted on prevention of T2DM specifically after GDM. There are a small number of pilot randomised controlled trials (RCTs) exploring the impact of lifestyle interventions on behavioural and metabolic markers. These studies have shown either no improvements [12]or some non-significant improvements [13-15], with one study finding a significant decrease in dietary fat intake in the intervention group [14]. These are largely pilot studies, none of which were UK based and the interventions were not modelled in a GDM population prior to implementation.

- 1. **Why this group?**

We will target women with recent GDM, as the cumulative incidence of T2DM after GDM shows the largest increase in the 5 years following pregnancy [16]. In addition, women are more likely to have another pregnancy in this period rather than later, meaning an intervention could help prevent a further episode of GDM. We will recruit women during pregnancy, when they are in frequent contact with health services and are already activated in relation to their health behaviours. Women can be receptive to change in the period around childbirth, and an intervention at this time could offer additional information and support to address the child’s diabetes risk by encouraging healthy behaviours for the whole family.

- 1. **Current diabetes prevention interventions**

The current gold-standard model for diabetes prevention based on the interventions used in large national programmes, is detailed in the IMAGE guideline (Development and *Im*plementation of *a* European *G*uidelin*e* and Training Standards for Diabetes Prevention) [17] . While this guidline provides a model for lifestyle intervention including a supportive programme of behaviour change, our preliminary work indicates this approach needs to be adapted for women with previous GDM. Previous studies with women with GDM have demonstrated increased barriers to engaging in lifestyle interventions or healthy behaviours postpartum, including the emotional stress of adjusting to motherhood, lack of time and childcare responsibilities [18, 19]. Pilot studies exploring the impact of lifestyle interventions post GDM [12, 15] cited recruitment and retention as challenges, and another [13] found that women felt the intervention, which ran from 6 weeks to 18 weeks postpartum, was too close to their baby’s birth. It is, therefore, important to adapt existing interventions to address the context of motherhood, and carefully consider the timing and delivery of the intervention to fit with the woman’s priorities. In addition, many of the general prevention intervention studies targeted older groups of people with impaired glucose regulation and are not congruent with the health perceptions and lifestyles to women with young infants. None of the pilot studies exploring lifestyle interventions for women with GDM were UK-based, and it is important to identify an intervention that is acceptable to the population group and can be easily translated into the NHS in a cost-effective manner.

- 1. **Qualitative research**

We have carried out a meta-synthesis of current qualitative studies of women with GDM [20] as well as conducting our own qualitative work with interviews and focus groups involving 50 women with previous GDM. The data indicates that women are keen to receive individualised lifestyle support after the birth, and from their accounts we have elicited a number of important facilitators and barriers to their adoption of positive health behaviours. We have used these data to adapt our intervention to enhance its sensitivity to the target population.

**2. Trial objectives, design and statistics**

### 2.1. Trial Objectives

The aim of the study is to explore acceptability of a lifestyle intervention to improve diet, increase physical activity and promote weight loss in women with recent GDM with a view to preventing or delaying T2DM, and assess the feasibility of the trial prior to a larger clinical trial.

**2.2 Intervention**

GODDESS aims to prevent T2DM and further episodes of GDM by increasing healthy eating, physical activity and weight loss. It has been adapted from the IMAGE (Development and **IM**plementation of **A** European **G**uid**E**line and Training Standards for Diabetes Prevention) diabetes prevention toolkit, which is based on a synthesis of current evidence for diabetes prevention (Lindström et al., 2010)- <http://www.image-project.eu/pdf/final_version_of_toolkit-perfect.pdf>. The IMAGE toolkit includes intervention frameworks for screening and for population, community and individual level intervention. The GODDESS intervention focuses on individual level intervention. IMAGE utilises a theoretically grounded behaviour change model that aims to prevent T2DM by:

- improving dietary intake (by reducing fat and refined carbohydrate intake, and increasing fibre intake);
- increasing physical activity (to over 30 minutes of moderate activity per day);
- promoting weight loss (≥ 5% loss).

GODDESS has adapted this model to reflect the needs of women with GDM based on our research into their needs. These include: attending to the psychological response of a GDM pregnancy; tailoring interventions to reflect the stage in pregnancy and the developmental stage of the infant (e.g. breast feeding, infant weaning and being able to exercise with their infant); integrating diet and physical activity within the context of the infant, child and wider family life; contextualising women’s diabetes and health risks in relation to infant and family well-being; and considering the particular challenges that come with motherhood.

We have also adapted the activity and weight loss targets to reflect NICE guidance on weight loss and pregnancy (<https://www.nice.org.uk/guidance/ph27/chapter/1-recommendations#recommendation-3-supporting-women-after-childbirth>.). Our targets for physical activity during pregnancy have been modified to concord with the NICE guideline which states that: women who have not exercised routinely should begin with no more than 15 minutes of continuous exercise, three times per week, increasing gradually to daily 30-minute sessions. We have also amended the weight reduction target to state that weight loss should only be attempted at 6-8 weeks postpartum with the aim of ≥ 5% reduction by 12 months from that point. The pregnancy activity and dietary targets have also been informed by the findings of the UPBEAT study [21]. This study was undertaken by members of our team and targeted obese women in pregnancy and reported reduced gestational weight gain (GWG) and increased physical activity without any adverse events [22]. The intervention has been further adapted and designed following a structured format to facilitate adoption within current NHS care delivery systems. The target behavioral outcomes for each phase of the intervention are identified in table 1. These are the global targets, each woman will set their own individual goals.

| Table 1. Behavioural outcomes | | | |
| --- | --- | --- | --- |
| *Intervention Phase* | *Target behavioral outcomes* | | |
|  | *Physical Activity* | *Diet* | *Weight loss* |
| Pregnancy | 1. 15 minutes of moderate physical activity increasing to 30 minutes (brisk walking, swimming) 2. Walking increase by 20% aiming for 10,000 steps per day | 1. Increase: fruit and veg intake; whole grain foods. 2. Reduce snacks and sugary drinks, refined carbohydrates and portion sizes. 3. Eat breakfast. 4. No calorie targets will be set for pregnancy | Weight loss not applicable but relative GWG to be managed as per baseline BMI:  Baseline BMI 25-29, GWG ≤ 9kg; BMI ≥30, GWG ≤ 6kg*. |
| Early post-partum (0-3 months) | 1. 30 Minutes of moderate physical activity 3 times per week increasing to daily. 2. Walking 10,000 steps per day | 1-3 as per pregnancy +   1. Breast feeding 2. Daily calorie target = 1,200 (+330 if breast feeding). | 1-2KG weight loss per week from 2 months post-partum. |
| Up to first year of life | 1-2 as per early post-partum | 1-3 as per pregnancy +   1. Daily calorie target = 1,200 (+400 if breast feeding). | ≥5% weight loss from 2 months post-partum. |
| *= Cedergren, M. (2007) Optimal gestational weight gain for body mass index categories. Obstet Gynecol. 2007 Oct;110(4):759-64. | | | |

The intervention is comprised of 5 face to face interactions (60 minutes) across the antenatal and postpartum periods delivered using motivational interviewing (MI) techniques. The focus of the sessions are targeted to reflect the changing context of needs during pregnancy and the postpartum period. The intervention is supported by a facilitated ‘WhatsApp’ group, motivational text messages, a pedometer and a website. An overview of the GODDESS intervention is provided in figure 1.

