| Focus:   - Reflect on goals from Session 1 affirming what they have achieved and learning reflectively from their experiences, attending to self-efficacy defects and directing to ongoing goals. - Elicit health beliefs, fears and worries, what is going well and what has gone less well. - Elicit what the patient thinks will be important in reducing their risk after pregnancy. - Share ideas on prevention activities in first 3 months postpartum using prompt cards- reflect on infant and family health context. - Review pedometer use. - Set new SMART goals with patient on prevention activities for first 3 months postpartum. - Review use of WhatsApp group. - Record new patient goals on intervention database and update personal plan. - Explain follow-up support to be provided.   Materials:   - Prompt-card with menu of lifestyle areas for early postpartum, including healthy eating tips, breast feeding and strategies for being active with a young infant.   Targets:   - Patient remains motivated and engaged. - Patient identifies 0-3 month postpartum diet and activity goals. - Patient is using pedometer and WhatsApp group. |
| NB. Pregnancy outcomes will be reviewed prior to progression to session 3. |
| **Session 3: 3 months postpartum (60 minutes)** |

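### Table 1 of section 2.2 gives the 0-3 month calorie target no start time, against a text that holds weight loss back to 6-8 weeks postpartum, and its weekly loss rate is hard to reconcile with the 12-month aim

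*Protocol*

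**What the plan says.** Section 2.2 of the Protocol sets the postpartum weight rule in its text: "weight loss should only be attempted at 6-8 weeks postpartum with the aim of ≥ 5% reduction by 12 months from that point".

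Table 1 (behavioural outcomes), in the same section, then gives targets by phase:

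- **Pregnancy.** Weight loss is marked as not applicable, and the diet cell says "No calorie targets will be set for pregnancy".
- **"Early post-partum (0-3 months").** The diet cell says "Daily calorie target = 1,200 (+330 if breast feeding"), with no start time. The weight-loss cell of the same row says "1-2KG weight loss per week from 2 months post-partum".
- **Up to the first year.** The diet cell says "Daily calorie target = 1,200 (+400 if breast feeding"), and the weight-loss cell says "≥5% weight loss from 2 months post-partum".

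The text introduces these as global targets, within which each woman sets her own goals. In section 4.4, session 2 includes this task: "Set new SMART goals with patient on prevention activities for first 3 months postpartum". The flowchart in section 2.3 places session 2 at 33-37 weeks' gestation and session 3 at 3 months postpartum.

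**The concern.** The text is restrictive: no attempt at weight loss until 6-8 weeks after birth. A calorie target that covers the whole 0-3 month phase is hard to square with that. The weight-loss cell beside it carries a delayed start and the calorie cell does not, so the table gives no sign that the calorie target is also meant to wait.

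The second difficulty is speed. The text gives a minimum percentage and a deadline a year away. The table gives a weekly rate in kilograms that would usually use up that minimum within weeks.

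The women concerned have just given birth, and some are breast feeding. Someone working from the text and someone working from the table could reasonably give them different advice about when to restrict intake and how fast to lose weight. This is an inconsistency in the table that defines the intervention's targets.

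**Working it through.** The Protocol derives no figure here that could be reproduced. The check is a comparison of passages plus simple arithmetic.

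**Inputs from the Protocol (section 2.2):** earliest weight loss 6-8 weeks postpartum; aim of at least 5% by 12 months from then; calorie target in the 0-3 month row, undated; 1-2 kg per week from 2 months; at least 5% from 2 months in the later row. Section 3 ends follow-up at 9 months postpartum.

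**Assumption:** the Protocol gives no body weight, so 50-140 kg is used as a range.

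**Conversion:** 1 month = 365.25 / 12 / 7 = 4.35 weeks.

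**Step 1, timing.**
- Start of the weekly rate: 2 × 4.35 = 8.7 weeks. This respects the 6-8 week rule.
- Start of the calorie target as written: week 0. This is 6-8 weeks before the text allows weight loss, and 8.7 weeks before the same row's weight-loss start.

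**Step 2, is the calorie figure a weight-loss target?** Table 1 does not say so. Two features point that way. Where weight loss does not apply (pregnancy), no calorie target is set. Where the 5% target applies (the later row), the same base of 1,200 appears.

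**Step 3, pace.** Weeks to reach 5% = 0.05 × weight / rate. Loss between 2 and 3 months = 4.35 weeks × rate = 4.3 kg at 1 kg/week and 8.7 kg at 2 kg/week.

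| Assumed weight | 5% of weight | Weeks at 1 kg/week | Weeks at 2 kg/week | Share lost from 2 to 3 months |
| --- | --- | --- | --- | --- |
| 50 kg | 2.5 kg | 2.5 | 1.25 | 8.7-17.4% |
| 80 kg | 4.0 kg | 4.0 | 2.0 | 5.4-10.9% |
| 100 kg | 5.0 kg | 5.0 | 2.5 | 4.3-8.7% |
| 140 kg | 7.0 kg | 7.0 | 3.5 | 3.1-6.2% |

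At 1 kg/week, the month from 2 to 3 months alone meets 5% for any weight up to 4.35 / 0.05 = 87 kg. At 2 kg/week it does so up to 8.7 / 0.05 = 174 kg.

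**Step 4, horizon.** Twelve months (52.18 weeks) from 6-8 weeks ends at (6 + 52.18) / 4.35 = 13.4 to (8 + 52.18) / 4.35 = 13.8 months postpartum. That is later than the first-year row of Table 1 and later than the end of follow-up.

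**The case against.** The best defence is that Table 1 lists broad targets by phase. The 0-3 month label names a phase and not a start date, the neighbouring cell dates weight loss from 2 months, and individual goals are left to each woman. That shows a charitable reading is available. It does not supply the missing start time, and the global targets remain the stated reference. The intervention overview figure is not reproduced in the copy reviewed, so it cannot be checked for a start time.

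Several stronger readings are tempting, and the document does not support them:

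- *The 2-month start of the weekly rate also breaks the timing rule.* It does not: 8.7 weeks falls after the 6-8 week window.
- *The weekly rate flatly contradicts the 12-month aim.* The aim is a minimum with a deadline, so faster loss satisfies it. Spreading 5% evenly over a year to obtain a multiple would treat a floor as a pace, which the Protocol never does.
- *Educators will apply 1,200 kcal from birth.* Session 2 covers goals for the first 3 months, but its content names no calorie figure. Weight is first discussed at session 3. Section 2.2 describes the behavioural focus as drinks, snacks, portions and activity.
- *The women are unsupported in this window.* No face-to-face session is scheduled between session 2 and 3 months, but there is remote support through the messaging group, texts and website, and section 6 provides incident logs and weekly team meetings.
- *Fidelity scoring or the 3-month weight result is compromised.* The contents of the fidelity checklist are not given, and no such effect can be shown from the document.

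**Conclusion.** The plan is wrong as written on one point and poorly aligned on another. The calorie target in the 0-3 month row has no start time and, read literally, runs 6-8 weeks ahead of the text's limit on weight loss. This rests on the inference that the target serves weight loss, which the rest of the table supports well. The rate of 1-2 kg per week is hard to reconcile with at least 5% by 12 months: over assumed weights of 50-140 kg the minimum would be reached in about 1-7 weeks. That second point is a mismatch between targets, not a logical contradiction. The matter bears on the safety of recently delivered women and should be settled before recruitment. The document does not show which of the passages is the intended one.

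**What to change.** Before the first participant, reconcile the section 2.2 text with both postpartum rows of Table 1 on three items: when the calorie target starts, the weekly rate of loss, and the overall weight-loss target with its horizon. Use the reconciled wording in the session materials. Neither the text nor the table should be presumed correct; which values apply is for the clinical team to decide. The cost is an edit to the Protocol and the session materials, with no added visits, measurements or participants.

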***Figure 1. Overview of GODDESS intervention***

***
[figure not shown]
***

***2. Theoretical framework and behaviour change techniques.***

GODDESS is underpinned by the following theoretical models for behavior change described in the IMAGE prevention toolkit. These include: the theory of planned behaviour and social cognitive theory. These models are integrated into a ‘self-regulatory’ framework incorporating: motivation; specific goal-setting; an action plan; feedback on performance; and goal review (Greaves et al, 2011)- see figure 2.

***Figure 2. Behaviour change model***

[figure not shown]

GODDESS also incorporates the 12 behaviour change techniques (BCT) identified Abraham & Michie’s (2008) BCT taxonomy:

- Provide information on consequences
- Prompt intention formation
- Prompt barrier identification
- Prompt specific goal setting
- Prompt review of behavioural goals
- Prompt self-monitoring of behaviour
- Teach to use prompts or cues
- Agree on behavioural contract
- Use follow-up prompts
- Plan social support or social change
- Relapse prevention

The principal technique used to deliver the theoretical model and BCT for GODDESS is motivational interviewing (MI). MI is a method that works on facilitating and engaging intrinsic motivation within the person within a co-productive (intervention provider and recipient) relationship in order to change behavior. MI is a goal-oriented, client-centered counseling style for eliciting behavior change by helping the person to explore and resolve ambivalence (Miller and Rose, 2009). MI is a proven approach for achieving weight loss in those who are overweight or obese (Armstrong et al, 2011). We are using MI to enhance the engagement of the women in making lifestyle change by: increasing their desire for change; addressing and reducing resistance to change; developing their confidence (self-efficacy) and commitment to change; setting realistic SMART goals with an individual action plan; reflecting and learning on goals; and by eliciting and mobilising social support and other resources to help them achieve and sustain change. All the face-to-face sessions will be conducted following an MI approach. These sessions will supplemented by the GODDESS e-support system which has also been designed following the same principles for behavior change with motivational feedback on performance, prompts and cues to action (see appendix 1). The active psychological mechanisms/techniques and their relationship to the overall behavior change model for GODDESS are detailed in Figure 2.

[figure not shown]

| **Key for techniques** | |  |
| --- | --- | --- |
| **EPE** | **‘Elicit, Provide, Elicit’** | |
| **OARS** | **‘Open questions, Affirmations, Reflections, Summaries’** | |
| **EE** | **‘Express Empathy’** | |
| **RR** | **‘Roll Resistance’** | |
| **DD** | **’Develop Discrepancy’** | |
| **SS** | **‘Support Self-efficacy’** | |
| **SMART** | **Simple, Measurable, Achievable, Relevant, Time based** | |
| **SCT** | **Social Control Theory** | |

The GODDESS intervention also incorporates the following specific lifestyle enhancement approaches: the frequency intensity time type (FITT) activity framework; specific dietary principles for short term weight loss and for maintenance; ‘eat clever’ principles; and recording and monitoring activities (Greaves et al, 2011). To enhance the physical activity element of the intervention the women will be given a pedometer with individualised step targets. The pedometer is delivered by a wearable technology that communicates with the e-support system to allow the women to see their progress and to trigger motivational feedback. Again there is evidence from meta-analyses of clinical trials showing that pedometers can increase activity and enhance weight loss, their effect is greatest when embed in a broader intervention of intervention such as GODDESS (Richardson et al, 2007; Bravata et al, 2007). Prompt and option cards with simple visual images are used to trigger discussion and help women consider their individual goals.

Consideration has also been given to socio-cultural adaptability of the intervention as it will be implemented in a range of different populations. The key strategies for this are to target transferable behavior patterns related to common lifestyle behaviours of relevance to all populations and to draw on the expertise of the educators to consider local and individual level factors related to the women’s socio-cultural contexts. The core principle is to keep behavioral goals simple and relevant and to support the women to identify strategies that work for them. In terms of behavioural goals the focus is on: the consumption of high energy drinks, reducing between meal snacks; reducing portion sizes; and increasing physical activity in their everyday routines. The educators will also be able to help women identify local resources (such as fitness programmes) that are appropriate to their cultural references.

